### 2.7 Anesthesia management

An identical anesthesia management technique will be used for all patients. Upon admission to the operating room, continuous monitoring of the patient’s vital signs will commence, including ECG, non-invasive blood pressure, HR, and oxygen saturation. Subsequently, peripheral venous access will be established, and invasive blood pressure monitoring will be initiated via femoral artery cannulation under local anesthesia. The nasopharyngeal temperature will also be monitored following intubation. Preoxygenation is a critical component of anesthesia induction. This involves the administration of intravenous propofol at a dosage of 2 mg/kg, sufentanil at 0.25 μg/kg, and rocuronium at 0.6 mg/kg. Following endotracheal intubation, we will utilize a combination of intravenous and inhalational anesthesia. Desflurane will be set at 0.4 MAC, and propofol will be maintained between 2–4 μg/mL to ensure that the bispectral index values remain within the range of 50–60. This parameter will serve as an indicator for monitoring the depth of anesthesia. The ventilation mode is configured for volume control ventilation, with adjustable parameters that include an FiO_2_ level of 60%, a tidal volume (VT) ranging from 6 to 8 mL/kg, and a respiratory rate set between 10 and 15 breaths per minute to maintain end-tidal carbon dioxide levels within the range of 35–45 mmHg. Given the extended duration of acoustic neuroma surgery, intraoperative monitoring of neurological function is imperative. Given that the use of muscle relaxants may interfere with this monitoring process, no additional muscle relaxants will be administered during the procedure. Before the skin incision, 5–10 μg of sufentanil will be administered to the patient based on their weight and current circulatory status. A routine dose of 10 μg of sufentanil will be given to the patient 30 min prior to the conclusion of surgery. Palonosetron (0.25 mg) will be administered prior to skin closure to prevent nausea and vomiting. Continuous infusion of remifentanil (0.15–0.3 μg/kg/min) will be utilized for intraoperative analgesia. This infusion will be gradually tapered off and discontinued 30 min before the end of surgery. The infusion rate of remifentanil will be adjusted to maintain mean arterial pressure (MAP) and HR within ±20% of the baseline values. During recovery, sugammadex will be employed for muscle relaxant antagonism. Intraoperative hypotension will be managed with ephedrine (6 mg) or epinephrine (40 μg). The treatment of bradycardia (<50 bpm) will involve the administration of atropine in a bolus dose of 0.01 mg/kg. If sympathetic excitation occurs, in addition to deepening anesthesia, nimodipine or esmolol may be used to maintain blood pressure and HR within normal ranges. Following the procedure, the patient will be transferred to the post-anesthesia care unit (PACU), where both anesthesiologists and nurse anesthetists will be responsible for the extubation and monitoring of the patient’s condition. The extubation criteria include achieving a VT of 5 mL/kg and a respiratory rate of 12 breaths per min, while ensuring that the patient awakens with a clear swallowing reflex. Additionally, oxygen saturation must remain at or above 95% after breathing room air for 5 min.

### 2.8 Follow-up

The follow-up period will last for 3 days after surgery. Assessments will be conducted at different time points, including pain VAS score, analgesic drug use and frequency, PONV score, postoperative rehabilitation quality score, postoperative hospital stay duration, and cost. Any perioperative adverse reactions related to the surgical procedure, anesthesia, or medication administration will be documented.

### 2.9 Pain management

Multimodal analgesic program:

(1)   Preemptive analgesia: preoperative pre-incisional infiltration anesthesia.(2)   Intraoperative: 10 ug of sufentanil and 50 mg of flurbiprofen will be administered before the end of surgery.(3)   Resuscitation room: pain control after recovery will be managed by the anesthesiologist in the resuscitation room. If the pain score is 4 or higher, 50 mg flurbiprofen will be given intravenously.(4)   Postoperative: oral celecoxib 200 mg twice daily will be chosen for postoperative analgesia. If the pain score is >4, 100 mg tramadol will be administered intramuscularly.

## 3 Outcome measures

### 3.1 Baseline data

Demographic characteristics include body mass index (BMI), age, sex, ASA status, acoustic neuroma size, and comorbidities. Surgical and anesthetic characteristics, including incision length, local anesthetic dosage, duration of surgery and anesthesia, intraoperative analgesic dosages (sufentanil and remifentanil), and hemodynamic parameters will be measured at five time points during the perioperative period.

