### 2.3 Recruitment and ethics

This study has been approved by the Ethics Committee of Shanghai General Hospital and registered with the Chinese Clinical Trial Registry (ChiCTR2400090509; Principal investigator: [name]; Registration Date: October 8, 2024). The trial protocol has been modified twice, with the final version being V3.0/20240715. This trial does not involve the collection of biological samples. Patients scheduled for acoustic neuroma surgery will be recruited and screened by the investigators 1 day prior to surgery. Those who meet the inclusion criteria will be scheduled for a subsequent interview, during which they will receive an informed consent discussion and will sign an enrollment form.

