#### 2.4.2 Exclusion criteria

(1)   Combination of severe cardiopulmonary, hepatic, or renal dysfunction(2)   History of mental illness or current use of psychotropic medications(3)   History of neurological diseases (e.g., cerebral infarction, transient ischemic attack, cerebral hemorrhage, Parkinson’s disease, intellectual disability, or craniocerebral injury).(4)   Heart rate (HR) <50 bpm or prolonged QT interval on electrocardiogram (ECG)(5)   ECG indicating pre-excitation syndrome or confirmed history thereof(6)   Allergy to ropivacaine or bupivacaine liposome(7)   Puncture site or systemic infection(8)   History of craniotomy(9)   Postoperative sedation for any reason.(10)   Inability to understand visual analog scores (VAS)(11)   Refusal to sign informed consent

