### 3.2 Primary outcome

The primary outcome is the 24 h postoperative pain VAS scores.

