## 4 Statistical methods and sample size

Data analyses will be performed using IBM SPSS Statistics version 20. In addition to the primary analysis, multivariable linear regression will be performed to adjust the primary outcome (24-h VAS score) for potential confounding variables, including age, sex, BMI, ASA physical status, duration of surgery, and tumor size. Exploratory subgroup analyses based on these factors will be conducted if the sample size permits. Normally distributed data will be reported as mean ± standard deviation (mean ± SD), while non-normally distributed data will be presented as median (N) with interquartile range. Categorical data will be shown as percentages (%). Pain scores at different time points will be compared using independent sample *t*-tests, and group comparisons will be analyzed using repeated-measures chi-square analysis. Other metrics will be assessed using χ^2^ tests, *t*-tests, or Mann–Whitney U tests as appropriate. A *p*-value < 0.05 will be considered statistically significant.

Based on prior literature (33), the parameters are set as follows: β = 0.2, α = 0.05, *R* = 1, μ1 = 2.9, μ2 = 3.7, and σ = 1.4. The sample size is calculated using PASS 15.0 statistical software, resulting in 50 effective cases per group. Considering the potential sample loss of 10% and the block size, 112 patients will be enrolled in this study.

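### No pain VAS is taken before surgery, so the 24 h VAS cannot be adjusted for pre-existing pain; the cost is precision and interpretability, not bias

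*Protocol article*

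**What the plan says.** Section 3.2 of the protocol article defines the endpoint as a single postoperative score: "The primary outcome is the 24 h postoperative pain VAS scores". In Table 1 the pain VAS row is marked at PACU, 24 h, 48 h and 72 h; the -1 day and 0 day cells are empty. Table 1 also has a general baseline row, marked at -1 day and 0 day, whose content section 3.1 sets out. For patient characteristics it reads: "Demographic characteristics include body mass index (BMI), age, sex, ASA status, acoustic neuroma size, and comorbidities". The rest of that section covers surgical and anaesthetic data. No pain score appears.

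Section 4 compares the groups on raw scores ("Pain scores at different time points will be compared using independent sample" *t*-tests). In addition to that primary analysis it plans a multivariable linear regression of the 24 h VAS on "potential confounding variables, including age, sex, BMI, ASA physical status, duration of surgery, and tumor size".

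The visit at which a score could be taken already exists. Section 2.3 says: "Patients scheduled for acoustic neuroma surgery will be recruited and screened by the investigators 1 day prior to surgery". Exclusion criterion (10) in section 2.4.2 is "Inability to understand visual analog scores (VAS"). None of the eleven exclusion criteria concerns pre-existing headache, chronic pain or regular analgesic use.

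**The concern.** A pain score at 24 h mixes pain from the operation with any pain the patient already had. With no preoperative value on the same scale, the two cannot be told apart in a patient, and the arms cannot be compared on pain at entry. Allocation is unstratified (section 2.5), so a chance imbalance in pre-existing pain could neither be shown in the baseline table nor adjusted for.

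The authors already intend to adjust the 24 h VAS for prognostic variables, and the same scale before surgery is a natural candidate that the list omits. The plan gives other outcomes a preoperative reference: MAP and HR are taken before anaesthesia, and a preoperative Apfel score accompanies PONV (section 3.3). The primary outcome has none.

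This is not a detail that a later analysis plan could supply. The article fixes the schedule, the baseline list and the covariates, and all three agree in the omission. A value that was never collected cannot be added at analysis.

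**Working it through.** **Inputs from section 4:** "β = 0.2, α = 0.05, *R* = 1, μ1 = 2.9, μ2 = 3.7, and σ = 1.4"; 50 evaluable per group; 10% loss; 112 enrolled. The difference is 3.7 − 2.9 = 0.8. Block length 8 is from section 2.5.

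**Input not in the documents:** the correlation *r* between preoperative and 24 h VAS. It is an assumption, shown at 0.2, 0.3 and 0.5.

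**Step 1: the plan's own figure.** By the normal approximation, two-sided, n = 2(1.96 + 0.84)² × 1.4² / 0.8², which rounds up to 49 per group. The exact *t*-test gives 49.05, rounded up to 50. (One-sided would give 38, so the stated figure is two-sided.) Loss: 50 / 0.90 = 55.6, rounded up to 56 per group, or 112 in all, which is 14 blocks of 8. The figure reproduces and does not depend on a baseline VAS. Power of the *t*-test at 50 per group is 0.808.

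**Step 2: what a preoperative VAS would add to the adjusted estimate.** Residual SD = 1.4 × √(1 − r²). Power is that of a two-sided *t*-test at 0.05 with 50 per group and a difference of 0.8, using this SD.

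**Step 3: the part of the 24 h difference due to chance imbalance in preoperative VAS.** Its SD is r × 1.4 × √(2/50) = r × 0.28. The 95% range is ±1.96 times that.

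| r (assumed) | Variance removed, r² | Residual SD | Power, 50 per arm | Chance part, 95% range |
|---|---|---|---|---|
| 0 | 0% | 1.400 | 0.808 | – |
| 0.2 | 4% | 1.372 | 0.823 | ±0.11 |
| 0.3 | 9% | 1.336 | 0.843 | ±0.16 |
| 0.5 | 25% | 1.212 | 0.904 | ±0.27 |

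Against the design difference of 0.8, the last column is 14% (0.11/0.8) to 34% (0.27/0.8). This is not an extra error: it is already inside the standard error of the raw comparison, 1.4 × √(2/50) = 0.28. Adjustment would take it out.

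**Step 4: which analysis the power column describes.** It describes a model adjusted for preoperative VAS, relative to no adjustment. The planned primary test is the unadjusted *t*-test, whose power stays at about 0.81 whether or not the score is collected. The planned regression already has six covariates; any variance they share with preoperative pain would shrink the gain.

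**The case against.** The strongest reply is that nothing here is invalid. Allocation is 1:1 and randomised, so pre-existing pain is balanced in expectation and the raw 24 h difference is unbiased. Chance imbalance is covered by the standard error and the significance level. The sample size was set for an unadjusted comparison and meets its target. A postoperative score compared between randomised arms is a legitimate endpoint. All of this stands.

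It is also true that the size of the gain is assumed. The document gives neither the correlation nor the frequency of preoperative pain, and the disease symptoms named in its discussion are dizziness and tinnitus, not headache. At r of 0.2 to 0.3 the gain in power is only 0.015 to 0.035. Recording comorbidities, and excluding psychotropic drug use, prior craniotomy and neurological disease, may narrow the group with pre-existing pain, although none of these gives a VAS value.

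A reader might infer more than the text supports:

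- **That the primary comparison is confounded by pre-existing pain.** Randomisation rules that out in expectation.
- **That the trial is underpowered, or that collecting the score would raise the power of the primary test.** The *t*-test is unaffected.
- **That the scale is already explained and scored at screening.** Criterion (10) excludes patients who cannot understand it, but describes no check and no recorded score.
- **That preoperative pain is the strongest predictor of the 24 h score.** The document does not show this.

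What survives is that the omission is consistent across the schedule, the baseline list and the covariate list, and cannot be repaired after the data are in.

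**Conclusion.** The point holds as a worthwhile improvement rather than an error. Without a preoperative pain VAS the trial gives up some precision in its adjusted analysis, cannot show or correct a chance imbalance in pre-existing pain, and has a primary score less clearly readable as postoperative pain. The estimate stays unbiased and the sample size stands.

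The gain in adjusted power, from about 0.81 to between 0.82 and 0.90, rests on an assumed correlation of 0.2 to 0.5. It would be smaller if the six existing covariates carry part of that information or if few patients have pain before surgery. It becomes a gain for the primary test only if a baseline-adjusted model is made the primary analysis.

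**What to change.** 1. In Table 1, mark pain VAS at -1 day.
2. In section 3.1, list preoperative pain VAS among the baseline data.
3. In section 4, add preoperative pain VAS to the covariates of the planned regression of the 24 h VAS.
4. Optionally, if the authors want the precision in the main result, name the baseline-adjusted model as primary, before unblinding. Otherwise the *t*-test remains primary and unchanged.

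The cost is one number at an existing visit and three short wording changes; the enrolment target does not change. The drawback is that section 2.1 dates the trial to October 2024, so some patients may already be enrolled without the value. They should stay in the regression through a missing-baseline indicator or mean imputation, using one mean over both arms. The gain then shrinks in proportion to how many lack the score.

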### 3.2 Primary outcome

The primary outcome is the 24 h postoperative pain VAS scores.

### 3.3 Secondary outcome

(1)   Postoperative pain VAS scores: pain VAS scores at 48 h and 72 h postoperatively.(2)   Changes in vital signs: the MAP and HR at five time points: T1 (before anesthesia), T2 (at incision), T3 (during drilling of the skull), T4 (at skin closure), and T5 (at the end of the operation).(3)   Intraoperative and postoperative analgesic use: intraoperative and resuscitation room opioid use, postoperative opioid use on days 1, 2, and 3, and the number and dosage of celecoxib administered will recorded. Data will be statistically converted to morphine doses.(4)   Incidence of PONV: the preoperative Apfel risk score includes four items: female sex, history of PONV or motion sickness, non-smoking status, and history of opioid use. The incidence of PONV in patients with 0, 1, 2, 3, and 4 risk factors is 10, 21, 39, 61, and 78%, respectively. The Alfel risk score ranges from 0 to 4, with higher scores indicating a higher risk. PONV will be assessed using the VAS scale (0–10), where 0 indicates no nausea; 1–4 indicates mild nausea; 5–6 indicates moderate nausea; and 7–10 indicates severe nausea.(5)   Extubation time and PACU stay: time to extubation and duration of stay in the PACU after surgery.(6)   Length of postoperative hospitalization and costs: duration of postoperative hospital stay and associated costs during hospitalization.(7)   Postoperative rehabilitation quality assessment: the 15-item Quality of Recovery Scale will be used to assess postoperative rehabilitation quality. On the third day after surgery or prior to discharge, patients will be asked to complete a 15-question questionnaire (Table 2). Response options range from 0 to 10 points, with 0 indicating poor condition and 10 indicating excellent condition.(8)   Other postoperative complications: incidence and nature of other postoperative complications.

**TABLE 2 T2:** 15-item quality of recovery scale (QoR-15).

Question	Score (0–10)
1. Do you feel that your breathing is comfortable?	
2. Is your appetite good?	
3. Are you able to rest sufficiently and feel energetic as a result?	
4. How is your sleep quality?	
5. Are you able to take care of your personal hygiene independently?	
6. Are you able to have normal conversations with family and friends?	
7. Do you feel supported and cared for by the medical staff?	
8. Are you able to engage in normal work or household activities?	
9. Do you feel comfortable and able to manage your emotions?	
10. Do you feel generally happy?	
11. Do you have severe pain that affects your sleep?	
12. Do you have severe pain that is unbearable?	
13. Do you have nausea or vomiting?	
14. Do you feel tense or anxious?	
15. Do you feel sad or depressed?	

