**Methods:**

This single-center, double-blind, randomized controlled study will recruit 112 patients scheduled to undergo acoustic neuroma surgery. We will compare the effects of liposomal bupivacaine and ropivacaine on postoperative pain when administered via preincisional infiltration before surgery. The primary outcome is the pain score at 24 h postoperatively. Secondary outcomes include the incidence of postoperative nausea and vomiting, amount of postoperative analgesic consumption, changes in vital signs before and after skin incision, and postoperative recovery scale.

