### 2.6 Intervention description

The intervention in this study involves preoperative infiltration of the patient’s scalp incision by the neurosurgeon using a 22-gauge needle under sterile conditions. Neurosurgeons will prepare separate local anesthetics before surgery in the operating room. In Group B, 20 mL of the original bupivacaine liposome solution will be used and in Group C, 0.75% ropivacaine (4 mL) will be diluted to a total volume of 20 mL with normal saline.

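### Pre-treatment (T1) MAP and HR are listed as an outcome time point instead of the baseline to adjust T2–T5 for, which gives up precision on one secondary outcome

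*Protocol article*

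**What the plan says.** Section 3.3, item (2), is labelled as changes and gives the outcome as "the MAP and HR at five time points: T1 (before anesthesia), T2 (at incision" and so on, so that T1 stands on the same footing as T2 (incision), T3 (drilling), T4 (skin closure) and T5 (end of operation). The abstract describes the outcome as "changes in vital signs before and after skin incision". Neither place says which value a change is measured from.

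Section 3.1, headed as baseline data, also states that "hemodynamic parameters will be measured at five time points during the perioperative period". The five-time-point haemodynamics therefore appear both as baseline data and as an outcome.

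Section 2.6 describes the intervention as "preoperative infiltration of the patient’s scalp incision by the neurosurgeon using a 22-gauge needle under sterile conditions". It does not say outright that T1 comes first, but a reading taken before anesthesia would ordinarily precede a pre-incisional infiltration by the surgeon.

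Section 4 says "Other metrics will be assessed using" chi-square "tests, *t*-tests, or Mann–Whitney U tests as appropriate". The one regression it names is for the 24-h VAS, with six covariates, none of them a haemodynamic value.

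**The concern.** A value measured before treatment cannot respond to treatment. Its use in a randomised comparison is as a covariate that removes between-patient variation from the later values. Listed as one of five outcome times, with only unadjusted tests named, T1 is not put to that use.

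Two things follow. First, the T2–T5 comparisons carry baseline variation in their error term that the trial already has the data to remove. Second, if the generic tests were also applied at T1, they would test differences that randomisation makes null.

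The response to skin incision is a stated objective (section 2.2), and MAP and HR are its most direct measurements, so the precision of this comparison has some value. The point concerns efficiency and clear definition. It is not a matter of bias.

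**Working it through.** **Plan's own figure.** The article gives no effect, SD or power for MAP or HR. Its only calculation is for the 24-h VAS: difference 3.7 − 2.9 = 0.8, σ = 1.4, α = 0.05, β = 0.2. Two-sided, the normal approximation gives 49 per group and the t-test gives 50, with 80.8% power. Then 50/0.9 rounds up to 56, and 2 × 56 = 112 = 14 × 8. The stated 50 and 112 reproduce. Only n = 50 per group is carried forward.

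**Formulas.** Let ρ be the correlation of T1 with a later value, and assume equal SDs σ at both times. The variance of the group difference is:
- later value alone: 2σ²/n
- later value adjusted for T1: (2σ²/n)(1 − ρ²)
- change from T1: (2σ²/n) × 2(1 − ρ)

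The ratio of adjusted to change-score variance is (1 − ρ²)/[2(1 − ρ)] = (1 + ρ)/2. This is below 1 for every ρ below 1. The change score beats the unadjusted value only if 2(1 − ρ) < 1, that is ρ > 0.5.

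**Results.** ρ is assumed. Power is by noncentral t at 50 per group for an assumed effect of 0.5 SD, chosen only to give a scale.

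| ρ | Adjusted variance ratio | SE reduction | Change-score variance ratio | Power: unadjusted | Power: adjusted | Power: change score |
|---|---|---|---|---|---|---|
| 0.1 | 0.99 | 0.5% | 1.80 | 69.7% | 70.1% | 45.4% |
| 0.3 | 0.91 | 4.6% | 1.40 | 69.7% | 73.7% | 55.3% |
| 0.5 | 0.75 | 13.4% | 1.00 | 69.7% | 81.6% | 69.7% |
| 0.7 | 0.51 | 28.6% | 0.60 | 69.7% | 93.4% | 89.2% |

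**Where ρ might lie.** Section 2.7 says "The infusion rate of remifentanil will be adjusted to maintain mean arterial pressure (MAP) and HR within ±20% of the baseline values". As an illustration only, suppose T1 is that baseline and later values are uniform within the band. With assumed means of 95 or 75 and SDs of 8 to 15, simulation gives ρ of about 0.59 to 0.81. This cannot be taken as an estimate, for the reasons given under the objection.

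**If T1 were tested.** Five times and two variables make ten tests, of which two are at T1. At 0.05 each, the expected number of false positives from those two is 2 × 0.05 = 0.10. The chance of at least one is 1 − 0.95² = 9.75% if they are independent.

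**The case against.** The strongest reply is that the article does not say what it appears to be charged with.

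- **Testing at T1.** A reader might infer that two known nulls will be tested. No sentence says so. The section 4 rule is a menu of tests to be used as appropriate, and T1 may have been listed only as the reference for the changes. This stands: null tests at T1 are a possibility under the wording and not a stated plan.
- **Analysis-plan detail.** The choice between raw value, change score and covariate adjustment is often left to an SAP, and none is shown. This stands only in part. The article does name methods for its other outcomes, they are unadjusted, and it confines regression to the VAS.
- **The changes label.** If change from T1 is intended, T2–T5 are not compared raw. That does not remove the point, because a change score is never more precise than adjustment and is worse than no adjustment below ρ = 0.5.
- **Size.** A reader might apply the trial's 81% power to MAP and HR, but that figure belongs to the VAS. Nor does the ±20% rule fix a high ρ. Remifentanil stops 30 minutes before the end of surgery, so its titration cannot govern T5. Section 2.7 also allows other agents aimed at normal ranges common to all patients, and it does not identify its baseline as T1. This stands.
- **Dilution.** A reader might infer that including T1 shrinks the effect to 4/5 of its size. That holds only for a repeated-measures group main effect averaged over T1–T5. Section 4 attaches its repeated-measures clause to the pain scores.
- **Validity.** An unadjusted randomised comparison is unbiased, and its standard error already allows for chance imbalance at T1. This stands.

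**Conclusion.** The point holds as a minor improvement. Section 3.3(2) places a pre-treatment value among the outcome times, no reference is defined for the changes, and the tests named in section 4 make no use of T1 as a covariate. Adjustment is the better method at any non-zero correlation, apart from the negligible cost of one degree of freedom. The gain is slight at ρ = 0.1 (SE down 0.5%) and substantial at ρ = 0.7 (SE down 28.6%). Which applies cannot be settled from the documents.

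The conclusion rests on T1 preceding the infiltration, which is inferred from the sequence described. The change-score comparison also assumes similar SDs at T1 and later. The documents do not support saying that the trial plans null tests, that it loses a known amount of power, or that its haemodynamic comparison is biased. One secondary outcome is affected. The primary analysis, its α and the sample size are not.

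**What to change.** In section 3.3(2), state that T1 is the baseline and that T2–T5 are the outcome time points. In section 4, add that MAP and HR at T2–T5 will be compared between groups by ANCOVA with the patient's T1 value as covariate, or by one mixed model over T2–T5 with T1 as covariate. Report T1 by group descriptively, without a test. In section 3.1, limit the haemodynamic baseline entry to T1, so that the later values appear only as outcomes.

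The cost is a few sentences and one degree of freedom. The T1 values are already to be collected, the named software can fit the model, and no extra patients, visits or measurements are needed.

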### 2.2 Objectives

The main objective of this trial is to implement preemptive analgesia through pre-incisional infiltration with bupivacaine liposomes. We aim to investigate the effects of this method on patients’ pain scores from 1 to 3 days postoperatively and to assess the patients’ reactions to skin incision, opioid consumption, and quality of recovery, with the ultimate goal of validating the superiority of pre-incisional infiltration with bupivacaine liposome in postoperative pain management in patients undergoing acoustic neuroma surgery.

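### The only MAP and HR value before skin incision is taken awake, so the change at incision is mixed with induction and the opioid given before incision

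*Protocol article*

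**What the plan says.** Three places in the protocol article describe this outcome, and they do not match.

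- The Methods part of the abstract lists, among the secondary outcomes, "changes in vital signs before and after skin incision".
- Section 2.2 (Objectives) says the trial will "assess the patients’ reactions to skin incision, opioid consumption, and quality of recovery".
- Section 3.3, item (2), defines the outcome as "Changes in vital signs: the MAP and HR at five time points". The points are "T1 (before anesthesia), T2 (at incision), T3 (during drilling of the skull"), then "T4 (at skin closure), and T5 (at the end of the operation").

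Section 3.1 also refers to five haemodynamic time points. Table 1 marks MAP and HR only once, on the day of surgery, and adds no detail.

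Section 2.7 describes what happens between T1 and T2. Induction uses "intravenous propofol at a dosage of 2 mg/kg, sufentanil at 0.25 μg/kg, and rocuronium at 0.6 mg/kg". Intubation and maintenance with desflurane and propofol follow. A further 5–10 μg of sufentanil is given before incision, the amount depending on weight and circulatory status. The scalp infiltration (section 2.6) also precedes incision. On intraoperative analgesia, section 2.7 states: "The infusion rate of remifentanil will be adjusted to maintain mean arterial pressure (MAP) and HR within ±20% of the baseline values".

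**The concern.** A response to incision is a change from a stable anaesthetised state just before the cut to a value shortly after it. The abstract and the objectives lead the reader to expect that quantity. The schedule in section 3.3 has no reading in that anaesthetised state. Its list is closed and section 3.1 repeats the count of five, so this is not a detail that the article has merely left to a fuller document.

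At stake is what the trial may say about one of its stated objectives. If the T1-to-T2 change is reported as the reaction to incision, readers will credit to incision a change that also contains the move from awake to anaesthetised. If MAP and HR look alike in the two arms, the reason could be equal analgesia at incision, or unequal analgesia evened out by the remifentanil infusion.

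**Working it through.** The documents give no target difference, standard deviation or sample size for MAP or HR, so there is no planned figure to reproduce. The check sets the time points against the stated outcome.

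**Step 1: all pairs of readings.** Five points give 5 × 4 / 2 = 10 pairs.

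| Pairs | Number | What the difference spans |
|---|---|---|
| T1 with T2, T3, T4 or T5 | 4 | Awake to anaesthetised, pre-incision sufentanil, infiltration, incision, and for the later points further surgical stimuli |
| Pairs among T2, T3, T4 and T5 | 6 | Both readings at or after incision; those with T3 involve skull drilling, a different stimulus |

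No pair has one reading under anaesthesia before incision and the other shortly after it.

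**Step 2: does the meaning of T2 rescue it?** T2 is described only as being at incision.
- If it is read once the response has developed, the preceding reading is T1, awake.
- If it is read at the moment of the cut, before any response, it could serve as a pre-incision value. The next reading is then T3, during drilling, so T3 − T2 mixes incision with drilling.

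Under either reading the incision response is not isolated.

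**Step 3: what T2 − T1 contains.** Take T2 as read after the response has begun, and write

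T2 − T1 = A + S + R,

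where A is the change from awake to anaesthetised, S the effect of the sufentanil and infiltration given before incision, and R the response to incision. With a reading P immediately before incision, A and S lie in P − T1, and T2 − P is essentially R. Without P the terms cannot be separated within a patient.

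**Step 4: the comparison between arms.** Section 2.7 applies one anaesthetic technique to all patients, and section 5 keeps the intraoperative anaesthesiologists blinded. Randomisation makes A comparable between arms in expectation. A comparison at T2, or of T2 − T1, is therefore a valid comparison of everything that follows allocation up to T2. It is less specific to R. For T2 − T1 the variance is Var(A + S) + Var(R) + 2 Cov(A + S, R), which exceeds Var(R) unless the covariance is sufficiently negative. The documents supply none of these terms.

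**Step 5: titration.** If the baseline in section 2.7 is the T1 value (an assumption, since that section does not define it), the infusion aims to keep T2 between 0.8 × T1 and 1.2 × T1. A difference in analgesia can then appear partly as a lower infusion rate and only partly as a difference in MAP or HR. The ±20% range still leaves room for differences within it.

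**The case against.** The strongest reply is that section 3.3 is the operative definition. It asks only for MAP and HR at five points, and all five can be obtained. This stands. A reader might infer that the outcome cannot be computed at all, but the documents do not support that: T1 is before incision, so T2 − T1 is a literal before-and-after difference.

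Second, the shared anaesthetic protocol and the blinding mean that induction adds noise and not bias between arms, and a direct comparison at T2 needs no earlier reading. This also stands. It limits the criticism to specificity and precision.

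Third, sections 3.1 and 3.3 item (3) already collect intraoperative opioid use, including remifentanil, so an effect absorbed by titration would leave some trace. This stands in part: no dose or rate is specified for the interval around incision. It is enough to reject the reading that similar MAP and HR would be uninterpretable. They would be harder to interpret.

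Fourth, both arms receive an active infiltration, so no schedule of readings would show whether infiltration as such blunts the response. That is correct. The question the trial can ask is whether the two agents differ, and the extra reading serves that question.

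Finally, the exact moment of a reading may be left to the case report form. That answers the timing of T2. It does not answer the missing pre-incision point, because the published list is closed.

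**Conclusion.** The point holds in a limited form. The abstract and section 2.2 promise a response to skin incision, and the five points in section 3.3 cannot isolate it, because the only pre-incision value is awake. The T1-to-T2 change also carries induction, maintenance anaesthesia and a sufentanil dose that varies between patients. The comparison of arms remains valid. It is less specific to incision, and remifentanil titration may blunt it.

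The extra noise in T2 − T1 rests on the assumption that the induction-related change varies between patients and is not strongly offset by the incision response. A reader might want a figure for the lost precision. Any such figure would need standard deviations and a correlation that the documents do not give, so none is offered.

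The consequence is confined to one secondary outcome. The primary outcome, 24 h pain VAS, and its sample size of 50 per group (112 enrolled) do not depend on it.

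**What to change.** In section 3.3 item (2), add a recorded MAP and HR reading after induction and infiltration, immediately before incision, and change the count of time points there and in section 3.1 from five to six. State how long after incision T2 is read. Define the incision-response outcome as the post-incision minus the pre-incision value, compared between arms, and report it alongside the remifentanil rate over the same interval.

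If the reading cannot be added, or recovered from anaesthesia records, reword the abstract and section 2.2 to match section 3.3 (MAP and HR at five points) and make no claim about a response to incision.

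The cost is one extra reading per patient from the invasive pressure and ECG monitoring already in use, plus a change to the case report form and the wording. Treatment does not change. Patients already treated may have missing values if their records do not hold the reading; the number affected should be reported.
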